## Abstract

**Background:**

Irritable bowel syndrome (IBS) is reported by one in ten of the population accounting for up to 40% of new referrals to gastroenterology outpatients. Patients characteristically have abdominal discomfort and disturbed bowel habit. Diarrhoea-predominant IBS is characterised by frequent loose stools with associated urgency and abdominal cramps. Current symptomatic treatments can reduce bowel frequency but often fail to reduce discomfort.

Mesalazine is an anti-inflammatory drug used to treat patients with inflammatory bowel disease. There is one pilot study suggesting it may be beneficial to patients who have diarrhoea-predominant IBS but these findings need to be confirmed in a larger trial. The current study aims to test the effectiveness of mesalazine to reduce symptoms in diarrhoea-predominant IBS patients. The study will also investigate the mode of action of the drug, especially its impact on mast cell activation.

**Methods/design:**

This is a multicentre randomised, double-blind, placebo-controlled trial using a parallel group design. At least 108 participants with diarrhoea-predominant IBS will be recruited through at least six hospitals. The intervention is a 12-week course of 2g mesalazine granules taken up to twice a day. The comparator is a blinded placebo granule formulation.

Outcome measures include stool diaries, symptom questionnaires, stool and blood samples together with rectal mucosal biopsies. The daily stool diary will record stool frequency and form, urgency, bloating, abdominal pain and a global satisfaction with control of IBS scored each week. The questionnaires will assess bowel symptoms, while the samples and biopsies will be used to analyse underlying mechanisms of any response.

Primary outcome will be the average stool frequency during weeks 11 and 12 of the treatment period and will be compared between treatment arms using an analysis of covariance in the form of a general linear model incorporating baseline characteristics that are thought *a priori* to strongly predict outcome. The primary efficacy parameter will be the difference in mean frequency between treatment arms.

**Discussion:**

This report describes a randomised controlled trial that will provide evidence of any benefit of treating diarrhoea-predominant IBS patients with mesalazine. The results will be available toward the end of 2013.

**Trial registration:**

ISRCTN76612274

## Background

While the presenting complaints in IBS are usually abdominal pain and erratic bowel habits, at least half the IBS patients have an associated history of anxiety or depression and the presence of multiple unexplained physical symptoms otherwise known as ‘physical symptom disorder’ [1]. Patients often believe that stress aggravates their symptoms but there is a poor correlation between stress and symptoms on a day-to-day basis [2].

Evidence is accumulating that activation of mast cells can occur in stressed humans [3]. In diarrhoea-predominant irritable bowel syndrome (IBS-D) patients, mast cell numbers have been shown to be increased [4-7]. We propose that anxiety and chronic stressors increase the number of activated mast cells throughout the gut in IBS patients, thereby inducing the characteristic visceral hypersensitivity and abdominal pain. We hypothesise that mesalazine treatment, through its anti-inflammatory effects, will reduce the number of mast cells and, thereby, reduce abdominal pain and diarrhoea.

Older studies using cromoglycate, a mast cell stabiliser suggested benefit in those with evidence of allergy on skin prick testing but these studies were uncontrolled [8]. More recently there have been other smaller studies targeting mast cells with antihistamines such as ketotifen [9]. Although this reduced visceral hypersensitivity, it had no effect on mast cell numbers or release of mast cell mediators. Our own trial of prednisolone in post infective IBS showed no benefit for IBS symptoms but was of limited duration at just three weeks. It did however show a fall in mast cell numbers in patients on prednisolone compared to patients on placebo, but the difference was not significant probably because the study was underpowered [10]. A strategy that reduces mast cell numbers over the long term might well be more effective than specific inhibitors of mast cell activation or indeed any specific mast cell products since these are numerous, all with quite variable modes of action.

The first open-label trial of 12 patients with IBS-D who responded to mesalazine [7] showed a benefit that took about two to three months to become apparent. There have since been three further reports of open-label treatment [11,12] and two small randomised control trials [13,14]. All except the Corinaldesi trial [13] used patients with IBS-D. The Bafutto trial showed a reduction in stool frequency, stool consistency and abdominal pain but was uncontrolled [12]. The Andrews study involved just six patients but this showed that mesalazine decreased biopsy proteolytic activity. The Corinaldesi trial in unselected IBS patients showed a significant reduction of mast cell numbers, an overall reduction in inflammatory cells [13], and an improvement in general well being without altering bowel function significantly.

## Rationale for the current study

Studies in Nottingham over the last decade demonstrated the importance of anxiety and depression [15], which along with adverse life events, increase the risk of post-infective IBS (PI-IBS) [16]. The changes observed in PI-IBS are very similar to those in IBS-D, the predominant bowel disturbance being diarrhoea with a similar prognosis [17]. This work has been supported by others who have shown inflammatory changes in IBS-D patients who do not have a background of previous infection [18,19]. Increased gut permeability has also been shown in IBS-D [20], a feature thought to be the result of psychological stress and/or inflammation secondary to infection [21].

We hypothesise that, through its anti-inflammatory effects, mesalazine treatment will reduce abdominal pain and diarrhoea by reducing the number of mast cells and subsequent release of their mediators which increase gut permeability and sensitivity [22]. Mesalazine therefore, both by virtue of inhibiting other inflammatory pathways and by directly inhibiting mast cell pathways, may reduce mucosal immune activation. We plan to investigate the effect of long-term mesalazine on mast cell numbers, the chronic inflammatory cells, and the mucosal production of inflammatory cytokines IL-1β and TNF-α, as well as the mast cell enzyme tryptase.

## Methods/design

### Trial purpose

The purpose of the trial is to define the clinical benefit and possible mediators of the benefit of mesalazine in IBS with diarrhoea.

We will therefore evaluate symptoms (primarily bowel frequency) and markers reflecting mast cell activation and small bowel tone.

### Trial design

This is a multicentre, two-arm, parallel group, double-blind, randomised placebo- controlled trial comparing mesalazine with placebo in patients with diarrhoea-predominant irritable bowel syndrome. Trial consists of a screening visit to check initial eligibility and to take consent prior to the participant completing a two-week screening phase stool diary. If they continue to remain eligible they will be randomised to receive 12 weeks of active or placebo treatment, stratified by site. Both groups continue completing the stool diary during treatment and will have three telephone contacts and two visits prior to completion. Participants will be in the study for 14 weeks. Please see Figure 1 for more details.

**Figure 1 F1:**
[figure not shown]
Participant involvement.

### Trial objectives

The trial objectives were as follows:

1) To assess the effect of mesalazine on stool frequency.

2) To assess the effect of mesalazine on

·• Overall IBS symptoms

·• Mast cell numbers, mucosal lymphocytes and faecal tryptase activity

·• Release of mast cell mediators from rectal biopsies.

·• Small bowel tone by measurement of fasting small bowel water content using magnetic resonance imaging (MRI).

·•To assess ability of biomarkers (mucosal/MRI parameters) to predict treatment response

### Participant recruitment

Ethical approval for the study was obtained from the Oxfordshire Research Ethics Committee B, United Kingdom.

Participants were recruited from IBS clinics at the investigator’s hospital, or from lists of patients who have previously taken part in research studies and have indicated that they would like to be contacted about future relevant research projects. In addition, in conjunction with the local Primary Care Research Network, we approached general practitioners (GPs) to ask them to search their databases for eligible participants and send out letters of invitation along with a participant information sheet (PIS). Either way, the initial approach was from a member of the patient’s usual care team or from appropriately authorised research nurses. We also advertised in the local newspaper and information about the study was also displayed in the relevant clinical areas. Ethical approval was obtained for all advertisements or posters displayed.

Patients were eligible for the study if they provided written informed consent and if they: 1) were male or female patients aged 18 to 75 years; 2) had had a colonoscopy or sigmoidoscopy within the last 12 months to exclude microscopic or any inflammatory colitis. (If not, but they have had a negative colonoscopy within five years and symptoms are unchanged, then a sigmoidoscopy and mucosal biopsy of the left colon was deemed to be sufficient to exclude microscopic or any inflammatory colitis); 3) met Rome III criteria for IBS-D prior to screening phase; 4) had ≥25% soft (Bristol Stool Form Score [BSFS] score >4) and <25% hard (BSFS 1 or 2) stools during the screening phase, as indicated in the daily symptom and stool diary; 5) had a stool frequency of three or more per day for two or more days per week during the screening phase; 6) had satisfactorily completed the daily stool and symptom diary during the screening phase at the discretion of the investigator; and 7) if female and of child-bearing potential, willing and able to use at least one highly effective contraceptive method throughout the study. If (4) and/or (5) is/are not met but the results are considered atypical (as observed from medical history and patient recall) then the patient can be rescreen on one occasion only.

Rome III criteria for IBS-D [23] were used to evaluate effect of mesalazine on patients during course of study. These criteria are as follows:

Abdominal Pain or discomfort at least two to three days/month in the last three months (criterion fulfilled for the last three months with symptom onset at least six months prior to screening) associated with two or more of the following:

1) Improvement with defecation;

2) Onset associated with a change of stool frequency;

3) Onset associated with a change in form (appearance) of stool.

Patients were not eligible for the study if they: 1) were pregnant or breast feeding; 2) had prior abdominal surgery which may cause bowel symptoms similar to IBS (note appendectomy and cholecystectomy will not be an exclusion); 3) were unable to stop anti-muscarinics, anti-spasmodics, high-dose tricyclic antidepressants (that is, above 50 mg/day), opiates/anti-diarrhoeal drugs, NS-AIDs (occasional over the counter use and topical formulations were allowed), long-term antibiotics, other anti-inflammatory drugs or 5-ASA containing drugs; 4) were on selective serotonin re-uptake inhibitors and low-dose tricyclic antidepressants (that is, up to 50 mg/day) for at least three months previous and unwilling to remain on a stable dose for the duration of the trial; 5) had other gastro-intestinal diseases including colitis and Crohn’s disease; 6) had renal impairment, severe hepatic impairment or salicylate hypersensitivity; 7) were currently participating in another trial or had been in a trial within the previous three months; 8) in the opinion of the investigator were considered unsuitable due to inability to comply with instructions or 9) had serious concomitant diseases (for example, cardiovascular, respi-ratory, neurological *et cetera*).

Regarding (3) loperamide was allowed as a rescue medication throughout the trial, however if more than two doses/week were taken during the screening phase then the patients became ineligible, though they could be re-screened on one occasion only.

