#### Secondary endpoint

Clinical secondary endpoints during weeks 11 and 12 of the treatment period:

1) Average daily severity of abdominal pain on a 0 to 10 scale.

2) Days with urgency.

3) Mean stool consistency using Bristol Stool Form Score.

4) Global satisfaction with control of IBS symptoms as assessed from the answer to the question ‘Have you had satisfactory relief of your IBS symptoms this week? Yes/No.’

Mechanistic secondary endpoints during weeks 11 and 12 of the treatment period:

1) Mast cell tryptase release during 6-hour biopsy incubation

2) IL-1β, TNF-α, histamine and serotonin secretion during same incubation

3) Small bowel tone assessed by volume of fasting small bowel water

4) Fecal tryptase activity

5) Difference in primary outcome measure between those with different TNFSF15 polymorphism

Ancillary secondary endpoints during weeks 11 and 12 of the treatment period:

1) EuroQol-5D (EQ-5D)

2) Centers for Disease Control and Prevention Health-Related Quality of Life (CDC HRQOL4)

3) Hospital, Anxiety and Depression Scale (HADS)

4) Patient Health Questionnaire-15 (PHQ-15)

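### Exclusion 4 puts the three-month condition inside the exclusion, so recent starters of an SSRI or low-dose tricyclic are eligible with no stability requirement

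*Protocol article*

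**What the plan says.** The exclusion list in the Protocol article, Participant recruitment, opens with "Patients were not eligible for the study if they", so meeting any one item makes a patient ineligible. Item 4 applies to those who "were on selective serotonin re-uptake inhibitors and low-dose tricyclic antidepressants (that is, up to 50 mg/day) for at least three months previous" and who, in addition, will not keep the dose constant during the trial. The words that join the two conditions are "for at least three months previous and unwilling to remain on a stable dose for the duration of the trial".

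Other text that could bear on these patients:

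- Item 3 of the same list requires certain drugs to be stopped. Among antidepressants it names only "high-dose tricyclic antidepressants (that is, above 50 mg/day".
- Item 8 excludes those who "in the opinion of the investigator were considered unsuitable due to inability to comply with instructions".
- The inclusion criteria do not mention antidepressants.
- Definition of a protocol deviation names only loperamide and antibiotics taken in weeks 11 and 12.
- Trial design states "Participants will be in the study for 14 weeks", made up of two weeks of screening and 12 weeks of treatment.

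**The concern.** A minimum period of prior use is normally a condition for letting a patient on a background drug into a trial: the drug is tolerated if it is established and will be kept constant. Item 4 has the same ingredients, but the three-month period sits inside the exclusion and is joined by 'and' to the unwillingness clause. It therefore narrows the exclusion and exempts the less settled patients.

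A drug begun shortly before screening may still be taking effect, or may be changed, during the 14 weeks. Symptom diaries and HADS could move for reasons unrelated to mesalazine. Restricting these drugs at all shows that the protocol wants background antidepressant use held constant, and the printed rule does not achieve this for recent starters. Sites following the printed wording could also differ, some applying the apparent intent and some the literal text.

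**Working it through.** **Logic of item 4.** Let A be use for at least three months and B be unwillingness to keep a stable dose. As printed, a patient is excluded only if A and B both hold. I read the item as applying to a patient on either drug class; read strictly, its wording could even require both classes together.

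| Prior use | Willing to stay stable? | Item 4 as printed | If both conditions were required for entry |
|---|---|---|---|
| 3 months or more | No | Excluded | Excluded |
| 3 months or more | Yes | Eligible | Eligible |
| Less than 3 months | Yes | Eligible | Not yet eligible |
| Less than 3 months | No | Eligible | Excluded |

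The last row is the anomaly. Unwillingness to stay stable bars an established user but not a new one, and no sensible intent produces that result. The third row depends on what was intended, which is why the full protocol must be consulted.

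**Does another rule close the gap?** Item 3 does not reach SSRIs or low-dose tricyclics. Item 8 concerns ability to follow instructions, not how long a drug has been taken. The inclusion criteria and the predefined deviations are silent on these drugs. Nothing closes it.

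**Size for the primary endpoint.** The document gives no rate of antidepressant use and no effect of it, so two inputs are assumptions: a share p of 5% to 15% recent starters (about 5 to 16 of 108) and a shift d of 1 stool per day. The SD of 2.0, the target difference of 1.4 and the 108 patients (54 per arm) come from Sample size.

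- Added variance is p(1 − p)d². For p = 0.05: 0.05 × 0.95 × 1 = 0.0475. For p = 0.15: 0.15 × 0.85 × 1 = 0.1275.
- Against 2.0² = 4, this is 1.2% to 3.2%.
- Chance imbalance of 7 versus 3 such patients: (7 − 3)/54 × 1 = 0.074 stools per day. That is 0.074/1.4 = 5% of the target difference.
- The standard error of the unadjusted arm difference is 2.0 × √(2/54) = 0.385, so 0.074 is about 0.19 standard errors.

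**Effect on power.** The normal approximation for 80% power at the two-sided 1% level gives 2 × (2.576 + 0.842)² × 4/1.4² = 47.7 per arm. Inflated by 3.2%, this is 49.2. Both lie below the planned 54.

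**The case against.** The strongest reply is that this is a drafting slip in a summary. The article says that it is based on protocol version 3.0 and that the full document is available on request. Sites recruit from the full protocol, and the intended meaning can be guessed. This stands in part: the article cannot show whether version 3.0 carries the same wording. It does not dispose of the point, because the criterion is not abbreviated. Duration, dose limit and willingness clause are all printed, and the logic that joins them is wrong. Either the article misstates the rule or the rule is faulty.

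It can also be said that the effect is small and that the primary model adjusts for baseline stool frequency. Both are fair. The adjustment absorbs only what is already present in the screening diary, not a drug effect that develops later.

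Several stronger readings are tempting and are not supported:

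- A reader might infer that the whole item is reversed. Only the three-month clause is misplaced; the unwillingness clause points the right way for an exclusion.
- A reader might infer that anyone with a recent dose change escapes. A patient on the same drug for three months or more is still bound to stay stable from entry. Only past dose stability goes unchecked.
- A reader might infer bias in the treatment comparison. Drug use at entry precedes randomisation, so any imbalance is random error already reflected in the standard error.
- A reader might infer a larger effect on the mechanistic endpoint "histamine and serotonin secretion during same incubation", or on HADS. The document says nothing about SSRIs altering mucosal serotonin and gives no figures from which to size either effect.
- A reader might take the Background statement that "at least half the IBS patients have an associated history of anxiety or depression" as a rate of drug use. It reports history, not treatment.
- A reader might take item 3 as evidence of concern about all tricyclic use. It concerns high doses only.

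**Conclusion.** The point holds as a fault of eligibility logic. On the printed text, recent starters of an SSRI or low-dose tricyclic enter with no stability requirement, while established users are held to one. This conclusion rests on the wording alone and needs no numerical assumption.

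The consequence is modest: extra noise and possible chance imbalance in symptom and HADS endpoints. For stool frequency the illustrative size is 1% to 3% more variance, conditional on the assumed share and shift; for HADS no size can be given. No power or sample-size figure is affected. Whether any patient was enrolled under the faulty wording cannot be told from the article. The correction is worth making because it is cheap and removes avoidable variability, not because the primary result is in danger.

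**What to change.** Compare item 4 with the full protocol and reconcile the two. Then correct the logic so that the document's own two conditions, at least three months' prior use and willingness to keep the dose stable for the duration, must both be met for a patient on these drugs to enter, instead of both being needed to exclude. Make clear that the item applies to a patient on either drug class. No new rule on dose changes or step-downs is needed.

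The cost is one sentence: an amendment if the full protocol shares the wording, or a correction to the article if it does not. The downside is that a few recent starters are deferred until they qualify. The change does not address patients who begin one of these drugs after entry, and it acts only on patients not yet recruited.

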### The interventions

#### Mesalazine and placebo

A licensed mesalazine slow-release granule formulation (2g) was used (PENTASA®, Ferring Pharmaceuticals Ltd, West Drayton, United Kingdom.) A matching placebo granule formulation was also used. In order to maintain blinding, active and placebo granules were packaged in matching de-identified trial-specific foil sachets.

The trial dose was 2g once a day (one dose in the morning) for the first week of treatment, then, if the initial dose was tolerated, a step increase to 2g twice a day (one dose in the morning, one dose in the evening) for the remaining 11 weeks of treatment. If the current dose was not tolerated participants could reduce that dose or stop completely.

All dose adjustments were made in consultation with the local investigator. Compliance was recorded in the daily stool diary and from returned sachets.

### Randomisation and blinding

This was a double-blind study. Neither participant nor supervising doctor nor study nurse was aware of the treatment allocation.

Randomisation was based on a computer-generated pseudo-random code using random permuted bal-anced blocks of randomly varying size, created by the Nottingham Clinical Trials Unit (NCTU). The randomization was stratified by site with participants randomly allocated (1:1 ratio) to either mesalazine or placebo. Access to the master sequence of treatment allocations was confined to the NCTU IT Manager and the Nottingham University Hospitals NHS Trust Clinical Trials pharmacy.

Investigators/sites accessed the treatment allocation for each participant by means of a remote, secure, internet-based randomisation system developed and maintained by the NCTU. The sequence of treatment allocations was concealed until interventions had all been assigned and recruitment, data collection, and all other trial-related assessments were complete.

In the event of the need to break the code, usually due to clinical need, the date and reason for breaking the code were recorded in the eCRF. The code could only be broken by authorised personnel via the web-based eCRF or, in the event the system being inaccessible, the Nottingham University Hospitals NHS Trust Clinical Trials pharmacy kept a copy of the treatment allocations.

